## Abstract

**Introduction:** Some encouraging findings of Chinese herbal medicine (CHM) in management of idiopathic membranous nephropathy (IMN) obtained in the setting of clinical trials are hard to validate in the daily clinical practice due to a complicated treatment scenario of CHM in practice. The primary objective of this registry is to provide a description of treatment patterns used in management of IMN and assess clinical remission in daily practice in a Chinese population sample with IMN.

**Methods and analysis:** This is a prospective, multicenter cohort which will comprise 2000 adults with IMN regardless of urinary protein levels that will be recruited from 11 nephrology centers across China. The participants will be followed for up to at least 2 years. Primary outcome is composite remission (either complete remission or partial remission) 24 months after enrolment. The secondary outcomes are complete remission, partial remission, time to remission, no response, relapse, proteinuria, annual change of glomerular filtration rate, antibodies against PLA2R, and composite endpoint of 40% reduction of glomerular filtration rate, doubling of serum creatinine, end-stage renal disease, and death. Propensity score analysis will be used for matching and adjustment.

**Ethics and dissemination:** This study has been approved by the Ethics Committee of Guangdong Provincial Hospital of Chinese Medicine (BF2020-094-01). Results of the study will be published in both national and international peer-reviewed journals, and presented at scientific conferences. Investigators will inform the participants as well as other IMN patients of the findings via health education.

**Study registration**: ChiCTR2000033680 (prospectively registered).

## Introduction

Membranous nephropathy (MN) is an autoimmune disease that affects the kidney glomerulus. It is the leading cause of nephrotic syndrome in nondiabetic adults, counting for 20–37% in most ages and up to 40% in patients over 60 (Ronco and Debiec, 2015; Couser, 2017). The incidence of MN is 10–12 per million persons per year in Europe and the USA, (Maisonneuve et al., 2000), and a rising incidence has been reported in China (Zhang et al., 2017). Approximately 80% of the cases are idiopathic and 20% of them are pathogenically associated with other systematic diseases (i.e., secondary MN). Optimal supportive care and therapy are applied to all patients with idiopathic MN (IMN) (Floege et al., 2019). Immunosuppressive therapy is recommended for IMN patients at risk for progressive kidney injury (e.g. decreasing glomerular filtration rate [GFR]) or with severe life-threatening nephrotic syndrome (Floege et al., 2019). Glucocorticoids combined with cyclophosphamide or calcineurin inhibitors, as well as rituximab, are the major treatment regimens for IMN patients at different risks. They are effective and also accompanied with risks including toxic effects and a high incidence of relapse. For rituximab, the high cost is a large obstacle to acceptability for patients. Other medicines, such as botanicals which include Chinese herbal medicine (CHM), are also widely used in treating IMN in China (Xu et al., 2015).

Studies showed that CHM could be an alternative monotherapy or adjunctive therapy for adults with IMN. Two case reports suggested that 1 year treatment of the herb *Astragalus membranaceus* Fisch. ex Bunge alone was associated with complete remission in patients who were presenting with nephrotic syndrome and resistant to cyclosporine and mycophenolate (Ahmed et al., 2007; Leehey et al., 2010). A retrospective case series comprised of 15 IMN cases who did not respond to immunosuppressive therapies received 6 months treatment of Jian Pi Qu Shi formula, and 80% of them reached complete or partial remission on the 12th month after treatment (Shi et al., 2018). Chen et al. reported a randomized controlled trial that compared multi-ingredient CHM to conventional immunosuppression with prednisone and cyclophosphamide for IMN patients with nephrotic proteinuria (urinary protein excretion ≥3.5g/24h) (Chen et al., 2013). Composite remission (either complete or partial remission) showed a similar rate in the two arms at 48 weeks (73% vs. 78%) (Chen et al., 2013). Liu et al. compared the remission between IMN patients who received tripterygium glycosides tablets (compound of the herb *Tripterygium wilfordii* Hook.f.) plus prednisone and who received tacrolimus plus prednisone (Liu et al., 2015). Both composite remission (86.9% vs. 90.0%) and complete remission (52.2% vs. 46.7%) were similar between the two groups at 36 weeks (Liu et al., 2015).

These findings were obtained in the setting of clinical trials and need validation in daily clinical practice, as the treatment scenario of CHM is more complicated in practice than that in trials. Instead of a fixed formula or proprietary CHM used through the whole research period in clinical trials, prescriptions of CHM are individualized and changed flexibly based on syndrome differentiation or state of the illness in clinical practice. Therefore, we proposed the first registry-based cohort study of INM in China.

The aims of this registry-based cohort include (but are not limited to):

### The Primary Aim

• To summarize the treatment patterns in daily practice for IMN patients in China, and to evaluate the effectiveness in terms of clinical remission among IMN patients who receive different treatment regimens, including CHM, conventional drugs, as well as the combination of both therapies.

### The Secondary Aims

• To identify the potential biomarkers for IMN population and/or subgroup population with specific characteristics.• To investigate the relationship between population characteristics including Chinese medicine syndromes and tongue features in IMN patients and clinical outcomes.

## Materials and Methods

### Study Design

This is a multicenter prospective hospital-based cohort study, and has been registered with the Chinese clinical trial registry. (ChiCTR2000033680).

### Study Setting

In order to collect a representative sample, the nephrology departments in 11 tertiary-care hospitals across multiple regions in China will recruit and enroll patients continuously. The 11 study sites include Guangdong Provincial Hospital of Chinese Medicine, Guangdong Provincial Hospital of Integrative Medicine, The First People’s Hospital of Zhaoqing, Liuzhou Hospital of Chinese Medicine, and Yue Bei People’s Hospital in south China; Hubei Provincial Hospital of Traditional Chinese Medicine in southwest China; Jiangsu Provincial Hospital of Chinese Medicine and the First Affiliated Hospital of Anhui University of Chinese Medicine in east China; Heilongjiang Institute of Traditional Chinese Medicine and First Affiliated Hospital of Heilongjiang University of Chinese Medicine in northeast China; Shanxi Traditional Chinese Medicine Hospital in northwest China.

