## Discussion

This national-wide, prospective, observational registry provides a platform for multi-center longitudinal research in IMN. During the first 5-year research phase of the registry, it is expected to provide a description of treatment patterns in patients with IMN in China, and more than that, to provide an estimation of the clinical remission of this population undergoing various therapeutic regimens in daily practice.

Quality control is vital in clinical studies, especially in multicenter studies. Our multicenter registry uses EDC to collect data and promote the quality of the data. Instead of finding errors after the data collection period, EDC allows researchers to build logical checks and pre-fillable answers, which can reduce the number of errors in the data at the collection site. Further, EDC keeps all traces of operation to ensure the authenticity of data.

Several bias may occur in a cohort. The nature of the cohort study could induce the participant selection bias, such as referral bias. As all 11 centers that participated in the study are tertiary-care hospitals, patients recruited from the centers with a particular severity differ from those in the community or general population, especially among prevalent patients (i.e., individuals who have already been receiving treatments before enrollment). Considering the incidence of IMN and the availability of subjects, in order to recruit enough samples on time, our cohort will include both incident patients who are newly diagnosed and first initiated on treatments and prevalent patients. Subgroup analysis of incident patients and prevalent patients will be performed to investigate whether the results are robust among the whole sample and different risk of subgroups and overcome the referral bias. In addition, in order to minimize the risk of selection bias, a propensity score approach will be used to balance the baseline characteristics of the CHM group and conventional group.

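### With 9 of 11 sites being Chinese-medicine or integrative hospitals by name, a pooled description of treatment patterns cannot be taken as IMN practice in China

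*Protocol article*

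**What the plan says.** The Study Setting section gives the purpose of the site choice: "In order to collect a representative sample, the nephrology departments in 11 tertiary-care hospitals across multiple regions in China will recruit and enroll patients continuously". It then names all 11 hospitals by region.

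The Primary Aim begins "To summarize the treatment patterns in daily practice for IMN patients in China" and goes on to the effectiveness of CHM, conventional drugs and their combination. The Discussion calls the registry nationwide and says of its first phase that "it is expected to provide a description of treatment patterns in patients with IMN in China".

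On selection, the Discussion concedes that patients at these sites are unlike patients elsewhere: "As all 11 centers that participated in the study are tertiary-care hospitals, patients recruited from the centers with a particular severity differ from those in" (quote cut short; its comparison is with people outside such hospitals). It offers two remedies: subgroup analyses of incident and prevalent patients, and a propensity score to balance the CHM and conventional groups. The propensity score variables in the Statistical Plan are all patient characteristics. Neither that list nor the subgroup list contains site, region or hospital type.

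**The concern.** The descriptive half of the primary aim asks how often IMN patients receive CHM alone, conventional drugs alone or both. A hospital of Chinese medicine may well prescribe CHM more often than a general hospital. If so, a site list made up mostly of one type acts directly on the quantity being described.

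Regional spread does not answer this, because outside south China every site is a Chinese-medicine institution. A larger sample does not answer it either, since it narrows the interval around a figure that still depends on the site list. At stake is a statement about practice in China that the choice of sites cannot carry.

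**Working it through.** **Step 1: count the sites (Study Setting), classified by name only.**

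| Region as listed | Sites | Chinese-medicine or integrative | General |
|---|---|---|---|
| South | 5 | 3 | 2 |
| Southwest | 1 | 1 | 0 |
| East | 2 | 2 | 0 |
| Northeast | 2 | 2 | 0 |
| Northwest | 1 | 1 | 0 |
| Total | 11 | 9 | 2 |

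The total of 11 agrees with the article. In the south, "Guangdong Provincial Hospital of Chinese Medicine, Guangdong Provincial Hospital of Integrative Medicine" are one of each special type. The other three appear in "Hospital of Zhaoqing, Liuzhou Hospital of Chinese Medicine, and Yue Bei", where only Liuzhou is a Chinese-medicine hospital. Elsewhere, "Hubei Provincial Hospital of Traditional Chinese Medicine in southwest China" is the single southwest site and "Jiangsu Provincial Hospital of Chinese Medicine and the First Affiliated Hospital of Anhui University of Chinese Medicine in east China" are the two eastern ones. The remaining three, in the northeast and northwest, also carry Chinese medicine in their names. So 9/11 = 81.8% are Chinese-medicine (8) or integrative (1), and all 6 sites outside the south are Chinese-medicine institutions.

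**Step 2: how a pooled frequency depends on the mix.** Let w be the share of patients from Chinese-medicine or integrative hospitals, and let p₁ and p₂ be CHM use in those hospitals and in general hospitals. Then

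pooled share = w·p₁ + (1 − w)·p₂

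shift between sample and population = (w_sample − w_population)·(p₁ − p₂)

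The article gives none of w_sample, w_population, p₁ or p₂. All values below are assumptions. Equal enrolment per site gives w_sample = 9/11, and w_population is set at 0.20, so the multiplier is 0.818 − 0.200 = 0.618.

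| p₁ vs p₂ | Sample | Population | Shift |
|---|---|---|---|
| 90% vs 40% | (9×0.9 + 2×0.4)/11 = 80.9% | 0.2×0.9 + 0.8×0.4 = 50.0% | 30.9 points |
| 60% vs 50% | (9×0.6 + 2×0.5)/11 = 58.2% | 0.2×0.6 + 0.8×0.5 = 52.0% | 6.2 points |
| 50% vs 50% | 50.0% | 50.0% | 0 |

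The population share matters too. With w_population = 0.50 the multiplier is 0.318, and the first two shifts fall to 15.9 and 3.2 points.

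**Step 3: sampling error for comparison.** At the planned 2000 patients and a share of 80.9%, the simple 95% half-width is 1.96·√(0.809×0.191/2000) = 1.7 points. Such an interval would look precise but would say nothing about the site mix.

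**Step 4: do the stated remedies reach this?** Incident and prevalent subgroups split patients by disease history, and each subgroup still comes from the same sites. The propensity score makes treatment groups comparable for the remission analysis; it does not change how many patients are in each group. Neither alters a regimen frequency.

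**The case against.** The strongest reply has four parts.

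- **The link from hospital type to prescribing is not in the article.** It gives no CHM use by hospital type and no enrolment by site. The Introduction says CHM is widely used for IMN in China without limiting this to one kind of hospital. The plan also expects patients on conventional drugs alone, since they form the matched comparison group. This stands: the link is an assumption, and with equal use there is no shift.
- **The article is more modest elsewhere.** The Abstract speaks of a Chinese population sample, Study Design of a hospital-based cohort, and Interventions of evaluating CHM in real-world hospital care, for which sites that use CHM are a sensible choice. The Discussion admits selection and referral bias in general terms. Continuous enrolment and admission of all risk levels also support breadth. This stands in part: these passages soften the claim, but they do not withdraw the representative and national wording or mention hospital type.
- **No pooled national percentage is explicitly planned.** The breakdown of descriptive tables may be left to documents not shown. This also stands, so the missing breakdown is not itself the fault. The fault is a positive claim that the article's own site list does not support, and an analysis plan cannot make the listed sites representative of hospital types.
- **Adding hospital type to the subgroup list would not by itself help.** That list follows the outcome analyses and would not correct a treatment-pattern frequency. This is right, and the remedy belongs in the descriptive reporting.

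A reader might infer that hospital type is known to decide CHM prescribing, so that the description is certain to misstate practice in China by a large margin. The article does not show that. Nor does the site list by itself show bias in the remission comparison, which is a separate question.

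**Conclusion.** The concern holds as a limit on what the descriptive half of the primary aim can conclude. The count, 9 of 11 with both general hospitals in south China, comes straight from the article, and so does the national target. A pooled treatment-pattern frequency therefore cannot be taken as IMN practice in China unless CHM use is similar across hospital types or the sample's mix of hospital types matches the population's; the article shows neither.

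The size is unknown. Under the main assumptions (9/11 of sampled patients and 20% of the population in Chinese-medicine or integrative hospitals) it runs from zero to about 31 points, depending on the assumed gap in CHM use. The change is worth making because it concerns part of the primary aim and costs little.

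**What to change.** 1. Report the treatment-pattern description separately for Chinese-medicine or integrative hospitals and for general hospitals, and do not present a pooled figure as a national estimate.
2. In the aim, Study Setting, Discussion and conclusions, replace the representative, nationwide and in-China wording with: in the participating tertiary hospitals, mainly of Chinese medicine.
3. In the Discussion, name hospital type as a selection limitation beside tertiary referral and severity.

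Hospital type is known from the site, so no new data, visits or sites are needed. The price is a narrower claim and less precision for general hospitals. With equal enrolment they would contribute about 2000×2/11 = 364 patients. At an assumed 40% CHM use the simple 95% half-width is 1.96·√(0.4×0.6/364) = 5.0 points, and two hospitals from one region say little about variation between general hospitals.

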### Eligibility Criteria

Eligible candidates for the study are IMN patients of any risk levels to capture a broad spectrum of clinical presentations. Inclusion criteria include Chinese adults aged from 18 to 85 years old; diagnosis of biopsy-proven IMN or antibodies against phospholipase A2 receptor (PLA2R)-positive patients who are not associated with other diseases which cause secondary MN, such as systemic lupus erythematous, infections with hepatitis B virus, hepatitis C virus, or syphilis, sarcoidosis, and cancer. Patients with the following criteria will be excluded: patients with a GFR less than 15 ml/min/1.73 m^2^; patients with comorbidities including malignant cancers, decompensated cirrhosis, hematologic diseases, and mental diseases.

### Interventions

This observational study is designed to evaluate the effectiveness of CHM in a real-word hospital setting. Therefore, there are neither treatment protocols nor interference with therapeutic schedules for the included participants. But the information of therapeutic regimens will be collected to identify the exposure of CHM. Exposure of CHM includes either oral or intravenous administration proprietary CHM products and oral administration CHM formulas. Low, moderate, and high level of CHM exposure will be defined as the cumulative exposure time of CHM accounts for 25, 50, and 75% of individual follow-up time. The individual follow-up time will be from the baseline visit to the last visit or the end of the study.

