### Enrollment and Follow-Up

This study is designed to be a long-term longitudinally extensible cohort. The study aims to include 2000 Chinese IMN adults. The recruitment is estimated to take 42 months, from July 2020 until December 2023. The patients who meet the inclusion criteria will be enrolled continuously. Both incident patients and prevalent patients will be recruited by physicians in nephrology clinics and inpatient departments in 11 participating sites. Incident patients are individuals who are newly diagnosed and first initiated on treatments. Prevalent patients are individuals who have already been diagnosed as IMN and have been receiving treatments before the study. Meanwhile, the electronic medical record in 11 participating sites will be retrospectively screened to recruit the confirmed cases.

Individuals who are eligible and consent to participate will be invited to attend a baseline visit. Participants will be followed for up to at least 2 years. Participants who experience the primary endpoint (remission) will be continued to be followed up until the end of the study or death. The schedule of follow-up visits is presented in Figure 1. Follow-up visits will occur quarterly in the first year after enrollment and then semi-annually from the second year. The baseline, semi-annual, and annual follow-up visits in the first year and annual visits from the second year are required in-person visits. All other visits can be in-person or remote via telephone call or smartphone applications. In order to retain participants and minimize the number of dropouts and withdraws as well as the missing data, a reasonably flexible visit time window within a range of 4 weeks forward or backward from the scheduled visit day will be acceptable.

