### Outcomes

The primary outcome is clinical composite remission at 24 months after enrollment. Composite remission is defined as either complete remission (CR) or partial remission (PR). Secondary outcomes are CR, PR, time to remission (CR, PR, and CR or PR), no response, relapse, urine protein excretion, urinary protein creatinine ratio, serum albumin, annual change of GFR (GFR slope), PLA2R, adverse events, and composite endpoint of 40% reduction of GFR, doubling of serum creatinine, end-stage renal disease (ESRD), and death. The outcome variables and definitions are presented in Table 1.

**TABLE 1 T1:** Outcome variables and definitions.

Outcome variables	Definitions
Primary outcome	
Composite remission	Either complete remission or partial remission
Secondary outcomes	
Complete remission (CR)	A reduction of proteinuria to ≤0.3g/24 h accompanied by a normal serum albumin and a normal Scr. Beck et al. (2013)
Partial remission (PR)	At least 50% reduction from peak value of proteinuria to a level between 0.3 and 3.5 g/24 h, accompanied by an improvement or normalization of serum albumin and a stable Scr. Beck et al. (2013)
Relapse	The development of proteinuria ≥3.5 g/24 h after a CR or PR
Time to complete remission	Days from enrollment to CR
Time to partial remission	Days from enrollment to PR
No response	No reduction in proteinuria of at least 25% from baseline
Serum albumin	/
Urine protein excretion	Urine protein excretion within 24 h
Urinary protein-to-creatinine ratio (UPCR)	/
Antibodies against PLA2R	/
Doubling of serum creatinine	Doubling increase of serum creatinine from baseline
40% reduction of eGFR	A reduction in eGFR of 40% from baseline. Serum creatinine based eGFR is calculated using the Chronic Kidney disease Epidemiology Collaboration (CKD-EPI) equation
End-stage renal disease (ESRD)	eGFR ≤15 ml/min/1.73m^2^ or commencement of renal replacement treatment
Composite endpoint	ESRD or 40% reduction of eGFR or doubling of serum creatinine
eGFR slope	Annual change in eGFR

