### Statistical Plan

Attempting to ensure equivalence in baseline characteristics of participants between the CHM group and the conventional therapy group, a propensity score method will be performed. Variables involving age, sex, proteinuria, eGFR, serum albumin, uric acid, PLA2R antibody level, and pathological type will be included into the logistic regression model to calculate a propensity score for each participant. Participants who are exposed to CHM will be matched to those who receive conventional drugs alone based on the propensity score, using the greedy matching with a standard calliper width of 0.2 and without case replacement. Covariate balance of the matched cohort will be assessed using the mean standardized differences. When a |d| > 0.10, it is considered as an imbalance. Inverse probability of treatment weighting based on the propensity score will also be performed to evaluate the robustness of the matching results.

Baseline demographic variables will be presented as means, medians, or percentages, and using Chi-square test, independent t test, or Mann-Whitney *U* test, as appropriate. Outcomes of composite remission, CR, PR, no response, death, relapse, and composite endpoint will be analysed by using Chi-square test and logistic regression. Odd ratios and 95% confidence intervals will be estimated. Time to remission will be analysed by using Cox regression model, adjusting for gender, age, baseline proteinuria, GFR, PLA2R antibody level, uric acid, Chinese medicine syndrome, and propensity score.

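### CHM exposure levels are measured over the whole of follow-up, partly after the remission outcome, so the planned analysis by exposure level is open to reverse causation; the main CHM grouping also lacks a time anchor

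*Protocol article*

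**What the plan says.** **Exposure levels.** Under Interventions, low, moderate and high exposure apply when the "cumulative exposure time of CHM accounts for 25, 50, and 75% of individual follow-up time". The window is explicit: "The individual follow-up time will be from the baseline visit to the last visit or the end of the study". The subgroup list in the Statistical Plan includes these levels.

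**Follow-up.** Under Enrollment and Follow-Up, "Participants will be followed for up to at least 2 years", and participants who reach remission "will be continued to be followed up until the end of the study or death". On timing, "The recruitment is estimated to take 42 months, from July 2020 until December 2023".

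**Outcome.** "The primary outcome is clinical composite remission at 24 months after enrollment" (Outcomes). Table 1 counts time to complete and to partial remission in days from enrolment.

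**Main comparison.** "Participants who are exposed to CHM will be matched to those who receive conventional drugs alone based on the propensity score" (Statistical Plan). No date or window is given for being exposed or for receiving conventional drugs alone. The propensity score uses patient and disease characteristics, and the Cox model adjusts for similar covariates plus the score.

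**Link between disease and exposure.** The Introduction says that in practice CHM prescriptions are individualized and altered according to syndrome or illness state.

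**The concern.** An exposure that is to explain an outcome has to be fixed before the outcome occurs. Here the level includes treatment given after remission and, for anyone followed beyond two years, after the primary time point. A patient who remits and then stops CHM collects a low share. A patient who does not remit and stays on CHM collects a high one. Remission then determines the exposure level, not the other way round.

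At stake is the reading of the exposure-level results. The plan does not call them a dose-response analysis, but ordered low, moderate and high groups invite that reading. A gradient, including one in which more CHM appears to mean less remission, could arise with no CHM effect. Matching or adjusting on baseline values cannot remove it, because the distortion arises after baseline.

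Two smaller points go with this. The levels are single percentages, not ranges, so it is unclear where shares between the marks, or below 25%, belong. And the main grouping, with no stated time of assignment, could be settled by later treatment as well.

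**Working it through.** The plan gives no figure of its own on this point. The checks below use its timings, with assumptions marked.

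**1. How much of the exposure window lies after month 24**

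Inputs: 42 months of recruitment and at least 24 months of follow-up (Enrollment and Follow-Up). Assumptions: even enrolment, and a study end when the last patient reaches month 24. Follow-up F is then uniform from 24 to 66 months, mean 45.

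- Average share after month 24 = 1 − (24/42) × ln(66/24) = 1 − 0.571 × 1.012 = 0.42.
- Largest share = 1 − 24/66 = 0.64.
- If the study ends at 5 years (the Discussion mentions a first 5-year phase), F runs 18 to 60 months and the average is [36 − 24 × ln(60/24)]/42 = (36 − 21.99)/42 = 0.33, with a maximum of 1 − 24/60 = 0.60. That end date would leave the last patients short of two years.

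**2. One patient, two enrolment dates**

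Remission at month 12, CHM stopped at month 15:

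- followed 24 months: 15/24 = 62.5%;
- followed 66 months: 15/66 = 23%, below the lowest mark.

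Treatment and outcome are identical, yet the level differs. A non-remitter who stays on CHM scores 100% in both cases.

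**3. Exposure levels when CHM has no effect**

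Assumptions: exponential time to first remission with 70% by month 24 (monthly rate −ln(0.30)/24 = 0.050); F uniform on 24 to 66 months; users on CHM from baseline; no relapse. The share is time on CHM divided by F.

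| Stopping rule (assumed) | <25% | 25–50% | 50–75% | ≥75% |
|---|---|---|---|---|
| A. All stop 3 months after remission, or earlier at random (mean 36 months) | 84% | 77% | 46% | 12% |
| B. All stop 3 months after remission, no other stopping | 100% | 96% | 52% | 9% |
| C. Half as in B, half stop at random over follow-up | 87% | 84% | 63% | 41% |
| D. A quarter as in B, the rest at random over follow-up | 79% | 77% | 67% | 55% |
| E. Stopping unrelated to remission (mean 36 months) | 70% | 70% | 70% | 70% |

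Entries are 24-month remission. The true rate is 70% in every cell.

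**4. Cutting the window at month 24 only**

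A patient who remits at month 6 and stops at month 9 scores 9/24 = 37.5%, while a non-remitter on CHM throughout scores 100%. The level still depends on the outcome.

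**5. Main comparison when CHM has no effect**

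Same remission and follow-up assumptions, 40% on CHM at baseline, groups formed as ever versus never exposed:

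| How groups are formed, or why CHM is started (assumed) | Odds ratio | Rate ratio |
|---|---|---|
| Groups fixed at baseline (69.9% v 70.0%) | 0.99 | 1.00 |
| CHM added while unremitted, 1–2% per month | 0.61 to 0.43 | 0.76 to 0.63 |
| As above, counting only starts before month 24 | 0.74 to 0.59 | 0.85 to 0.75 |
| CHM started only after remission, 1–2% per month | 1.64 to 2.33 | 1.32 to 1.61 |
| Start unrelated to remission, 2% per month | 0.99 | 1.00 |

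The direction depends wholly on why CHM is started.

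**The case against.** **The whole-follow-up window is stated only for the three levels.** This stands. A reader might infer that the same window governs the main comparison and that its result is therefore biased. The Statistical Plan gives no window for that comparison, and its stated aim of balancing baseline characteristics between the groups is compatible with assignment at baseline. A condensed article may also leave time zero to a fuller document.

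**Immortal time is not the right label.** A reader might say that late CHM users must have stayed unremitted until they started. But remission does not end follow-up, so a patient can remit first, start CHM later and still count as exposed. Immortal time in the strict sense arises only if CHM is started solely while unremitted, or with respect to death. Conditioning on later exposure describes the problem better.

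**The steep gradients rest on an assumed stopping rule.** This stands too. Rows A and B are extreme cases, C and D are milder, and E shows none. What weakens E as a description of practice is the Introduction's own statement that prescriptions follow the patient's condition.

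**The level analysis is one of many subgroup analyses.** True, and it limits the reach of the explicit defect. It does not make that analysis interpretable.

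**Pooling of regimens.** A reader might object that the exposed group mixes CHM alone with the combination, although the primary aim names regimens "including CHM, conventional drugs, as well as the combination of both therapies". The subgroup list already plans an analysis of the three regimens, so this adds little.

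**Conclusion.** For the exposure-level analysis the concern holds on the text. Followed as written, exposure is measured partly after the outcome and, given prescribing that responds to illness, can be shaped by it. The false gradient may be large (84% down to 12%), moderate (79% down to 55%) or absent, depending on how far stopping follows remission, which the article does not quantify. The 42% average share of the window after month 24 rests on even enrolment and follow-up of 24 to 66 months; a 5-year end gives 33%.

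For the main comparison, the supportable point is narrower: the groups are not anchored in time, and baseline propensity matching could not correct a grouping settled by later treatment. The null odds ratios of 0.43 to 2.33 show what could happen under assumed start rules. They do not show that the plan's primary result is biased, or in which direction.

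**What to change.** 1. **Exposure level.** Count CHM time only up to remission or month 24, whichever comes first. Analyse it as a time-varying exposure, lagged to precede the outcome (Cox model with time-dependent exposure, or a marginal structural model), or classify exposure up to a landmark and count outcomes from there. Cutting at month 24 alone is not enough.
2. **Levels.** Write them as ranges that together cover 0 to 100%, with a stated place for shares below 25%.
3. **Main comparison.** State that CHM and conventional-only groups are assigned by the regimen in force at enrolment, or at an early landmark with follow-up counted from it.

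The cost is wording and some extra analysis. Cumulative exposure time already requires dated treatment records, so no new data should be needed, although the visit schedule figure is not available to confirm this. The downside is that later switching dilutes a contrast based on the regimen at enrolment; the time-varying analysis can be reported beside it.
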